### Interim analyses {21b}

Since no interim analysis or stopping guidelines have been planned. From the aspect of the benefit of the population, a stepped wedge design will be followed after this trial.

### Methods for additional analyses (e.g., subgroup analyses) {20b}

No subgroup analyses are planned.

### Methods in analysis to handle protocol non-adherence and any statistical methods to handle missing data {20c}

Since the intervention (ceiling net) will be installed in trial participants’ houses, participants not sleeping in their own houses will not benefit from the intervention. In the cohort, non-adherence to the intervention can be inferred from travel history during bi-weekly interviews. Therefore, participants who regularly sleep outside their homes will be removed from the analyses. The extent and patterns of missing data will be assessed once all data collection has been completed. If necessary, multiple imputation methods will be used to handle missing data.

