#### Criteria for discontinuing or modifying allocated interventions {11b}

Since the ceiling net is semi-permanently installed, the intervention will be discontinued only when the participant specifically requests the removal of the ceiling net by the study team. We do not allow any crossover from the control arm to the intervention arm during the follow-up period. Those who migrate between the arms or emigrate from the study areas will be dropped from the study follow-up.

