#### Strategies to improve adherence to interventions {11c}

Adherence to the intervention cohort in this study is defined as sleeping in houses with Olyset®Plus ceiling nets. Adherence is monitored indirectly by assessing the number of nights each participant spends outside their house during the bi-weekly interview. During each house visit, CHVs will visually inspect the condition of the ceiling nets. Any visible tear and damage to the ceiling net will be reported to the research team by the size and location of the damage.

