### Outcomes {12}

The primary outcome of the study is malaria prevalence by microscopy in schoolchildren (3 to 15 years old) 12 months after Olyset®Plus ceiling net installation. The secondary outcomes are (1) malaria prevalence by PCR in schoolchildren at 6 and 12 months post-installation; (2) cumulative malaria incidence in the prospective cohort for 12 months post-installation; (3) anemia prevalence in schoolchildren at 6 and 12 months post-installation; (4) prevalence and level of antibodies (IgG) against *Anopheles* salivary proteins gSG6 and cE5 in the prospective cohort at 6 and 12 months post-installation, as a measure of exposure to mosquito bites; (5) anopheline mosquito density, species composition, and sporozoite infection prevalence at 6 and 12 months post-installation; (6) the percentage of cohort participants who sleep under the bed net at 6 and 12 months post-installation; and (7) perception of the Olyset®Plus ceiling nets among community members.

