## Statistical methods

### Statistical methods for primary and secondary outcomes {20a}

The intention-to-treat (ITT) analysis is the primary analysis approach for both the primary and secondary outcomes, and the per-protocol analysis will be included as a supplementary analysis.

The primary outcome of the study is malaria prevalence by microscopy in schoolchildren (3 to 15 years old) 12 months after Olyset®Plus ceiling net installation. The results of microscopic examination from the cross-sectional survey 12 months after the implementation will be compared between the intervention arm and the control arm, based on cluster-level summaries using the two-stage procedure [27]. In the first stage, an individual-level logistic regression model will be constructed with adjustments for confounders, including age, gender, bed net use, house structure, and SES, and a fitting value will be summarized for each cluster using the model. In the second stage, a residual from the fitted values and the observed values for each cluster will be computed. The difference between the two groups will be tested using Wilcoxon’s rank-sum test by ranking cluster-level summaries.

As a secondary outcome, the malaria prevalence by PCR and anemia prevalence at 6 and 12 months after the implementation will be evaluated similarly. The cumulative malaria incidence during the 12-month follow-up will be analyzed based on the cohort follow-up data. Both symptomatic disease incidence and infection incidence, including asymptomatic infection, will be compared between the intervention and control arm based on cluster-level summaries. Entomological parameters, namely anopheline mosquito density, species composition, infection rate, and antibodies (IgG) against Anopheles salivary proteins gSG6 and cE5 at 6 and 12 months post-installation, will be analyzed in the same manner. Community members’ perceptions are analyzed qualitatively based on the questionnaire, focus group discussion, and in-depth interviews.

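### Section {20c} removes cohort members who sleep away from home from the analyses, although {20a} makes ITT primary, so as written the cohort outcomes would not be analysed by ITT

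*Protocol article*

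**What the plan says.** On the analysis set, section {20a} is unambiguous: "The intention-to-treat (ITT) analysis is the primary analysis approach for both the primary and secondary outcomes". The same sentence adds that "the per-protocol analysis will be included as a supplementary analysis".

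Section {20c} deals with non-adherence. It reasons that people who do not sleep in their own house cannot benefit from a net installed there, and continues: "In the cohort, non-adherence to the intervention can be inferred from travel history during bi-weekly interviews". From this it concludes that "participants who regularly sleep outside their homes will be removed from the analyses". Per-protocol is not mentioned in {20c}. On missing data, the section says: "If necessary, multiple imputation methods will be used to handle missing data".

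Two other sections bear on who is followed and who counts as adherent. Section {11c} states: "Adherence to the intervention cohort in this study is defined as sleeping in houses with Olyset®Plus ceiling nets". Section {11b} states: "Those who migrate between the arms or emigrate from the study areas will be dropped from the study follow-up".

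**The concern.** ITT keeps everyone in the arm to which their cluster was randomised, whether or not they were in a position to benefit. {20c} excludes people because they are not in that position, and does so on behaviour observed after randomisation. An exclusion of that kind belongs to a per-protocol analysis. Applied to the analyses in general, it contradicts {20a} and leaves little to separate the ITT cohort analysis from the supplementary one.

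The outcomes at stake are those that the Outcomes section {12} places in the cohort: cumulative incidence over 12 months, prevalence and level of IgG against mosquito salivary proteins, and bed net use. Cohort incidence is the first secondary objective and has its own sample size calculation. The Discussion also presents the trial as the first to study ceiling nets and infection incidence by active case detection. An analyst who follows {20c} and one who follows {20a} would report different estimates for it, and the choice could be made with the data in view.

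**Working it through.** **The rule and its reach**

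| Question | {20a} | {20c} |
|---|---|---|
| Which analysis? | ITT primary, per-protocol supplementary | The analyses, with no qualifier |
| Which outcomes? | Primary and secondary | Those from the cohort, identified by bi-weekly interview |
| Who is kept? | Everyone, by assigned arm (the meaning of ITT) | Not those who regularly sleep away |

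The two columns cannot both govern the main cohort analysis.

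**Inputs from Sample size {14}**

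- Control incidence: L0 = 2.0 per person-year.
- Intervention incidence: L1 = 1.2 per person-year.
- The plan's own figure reproduces: 1.2 / 2.0 = 0.60, a 40% reduction.

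**Assumptions, because the protocol gives no figures**

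- f = share of the cohort who regularly sleep away, equal in both arms: 5%, 10%, 20%.
- r = incidence among away-sleepers divided by L0, the same in both arms.
- 1.2 is taken as the rate in people who sleep under the ceiling net, with equal person-time per participant.

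**Formulas**

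- ITT rate ratio = [(1−f)·L1 + f·r·L0] / [(1−f)·L0 + f·r·L0]
- Removed from both arms = L1 / L0
- Removed from the intervention arm only = L1 / [(1−f)·L0 + f·r·L0]

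**Removal from both arms, r = 1 (away-sleepers at the control rate)**

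| f | Intervention rate under ITT | ITT ratio | Ratio after removal |
|---|---|---|---|
| 5% | 0.95×1.2 + 0.05×2.0 = 1.24 | 1.24/2.0 = 0.62 | 0.60 |
| 10% | 0.90×1.2 + 0.10×2.0 = 1.28 | 1.28/2.0 = 0.64 | 0.60 |
| 20% | 0.80×1.2 + 0.20×2.0 = 1.36 | 1.36/2.0 = 0.68 | 0.60 |

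Reductions of 38%, 36% and 32% under ITT would each appear as 40%. With other values of r the ITT ratio runs from 0.605 (f = 5%, r = 0.25) to 0.709 (f = 20%, r = 1.5), always above 0.60. The reason is that the same amount, f·r·L0, is added to both numerator and denominator, which pulls a ratio below 1 towards 1. If the nets had no effect, removal from both arms would leave the ratio at 1.0.

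**Removal from the intervention arm only, f = 10%**

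| r | ITT ratio | Ratio after removal | Direction |
|---|---|---|---|
| 0.25 | 1.13/1.85 = 0.611 | 1.2/1.85 = 0.649 | against the nets |
| 0.6 | 1.20/1.92 = 0.625 | 1.2/1.92 = 0.625 | none |
| 1 | 1.28/2.00 = 0.640 | 1.2/2.00 = 0.600 | towards the nets |
| 1.5 | 1.38/2.10 = 0.657 | 1.2/2.10 = 0.571 | towards the nets |

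The turning point is r·L0 = L1, that is r = 1.2/2.0 = 0.6.

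**The case against.** The best defence is that {20c} is only describing the per-protocol set which {20a} has already called supplementary. That may well be the intention, and it is the natural repair. But {20c} does not say so, and section {31c} presents the article as the full protocol, so no fuller text can be assumed to settle it.

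The defence does limit the point. A reader might infer several stronger things that the document does not support.

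- **That the primary analysis is compromised.** Section {12} reads: "The primary outcome of the study is malaria prevalence by microscopy in schoolchildren (3 to 15 years old) 12 months after Olyset®Plus ceiling net installation". That comes from the school survey. The removal rule is introduced for the cohort and rests on interviews held only with cohort members.
- **That {11b} is itself an exclusion from analysis.** It ends follow-up for people who move. It does not discard what was already collected, {14} allows for 3% dropout per month, and {20c} allows imputation. Incomplete follow-up is weaker than a rule to remove people.
- **That removal falls on one arm.** {20c} speaks of participants without naming an arm, and the interviews ask all cohort members about travel. {11c} ties adherence to the intervention cohort because only that arm has nets to adhere to; it is not an exclusion rule.
- **That bias towards the nets is established.** The second set of results shows that the direction can reverse under one-sided removal.
- **That many people sleep away because of fishing.** The Study setting names fishing and farming together as primary occupations and links neither to nights away. Cohort eligibility also excludes people planning an absence of more than one month, which limits long stays away but not frequent short ones.

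**Conclusion.** The contradiction between {20a} and {20c} is real and should be resolved. It is confined to the cohort outcomes, all of them secondary.

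The likely consequence is an overstated effect relative to ITT: a reported rate ratio of 0.60 where ITT would give 0.62 to 0.68. This holds if 5% to 20% of each arm sleep away at the control rate and are removed alike from both arms. Those shares and that rate are assumptions, so the figures show the order of size and are not a forecast. Under removal from the intervention arm only, the sign turns on whether risk away from home is above or below 0.6 of the control rate, and the document does not settle that.

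**What to change.** In {20c}, state that the removal of people who regularly sleep away applies only to the supplementary per-protocol analysis, with the same sleeping-away rule in both arms. State also that the ITT cohort analysis keeps all enrolled cohort members under their assigned cluster. For people dropped under {11b}, add that they contribute the person-time and outcomes collected until they left, under the cluster to which they were assigned.

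The cost is a wording change. The interviews already ask all cohort members about travel, so no new data are needed. The cohort ITT estimate may be slightly smaller. One limit remains: cohort follow-up ended on December 16, 2022, so wording cannot recover data that were not collected after someone moved. Those participants are censored at the move, or handled by the imputation that {20c} already allows.

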### Plans to give access to the full protocol, participant-level data, and statistical code {31c}

This manuscript is the full protocol. The corresponding author will make the de-identified datasets or any future statistical code available upon reasonable request.

### Oversight and monitoring

#### Composition of the coordinating center and trial steering committee {5d}

The sampling team, composed of CHVs and laboratory technicians, set up a day-to-day communication group and exchanged their experiences. A local management team of study investigators from Kenya and Japan also joined this, leading and advising the activities and monitoring the sample and data integrity. A monthly meeting will be held by the steering committee composed of all key researchers from Kenya and Japan, including the principal investigator (PI) and co-PI, which aim to monitor the progress of the trial.

#### Composition of the data monitoring committee, its role, and reporting structure {21a}

Because this intervention is considered to be of a low-risk nature, this study does not have a data monitoring committee. For additional credibility about study quality, the researchers will consult a third statistician, if necessary.

#### Adverse event reporting and harms {22}

Neither the ceiling net nor the synergist PBO is known to pose significant health or safety risks. Nonetheless, all unanticipated problems will be reported to the research team and Homa Bay County Ministry of Health (MOH) through CHVs. Medical officers from Homa Bay County will assess the relatedness of the reported events to the study and report to the research team, including the PI. In the event of a study-related serious adverse event, the study team will convene a meeting immediately with the MOH and Homa Bay County Teaching and Referral Hospital representatives to review the case and take necessary action.

#### Frequency and plans for auditing trial conduct {23}

After participant recruitment, enrollment, and implementation of the intervention are completed, the research team will have a meeting to review the protocols for outcome evaluation. A monthly meeting will be held during the follow-up period to ensure that all surveys and investigations are conducted according to the study protocol. The study is required to submit annual reports and renewal to ethical review boards of Osaka Metropolitan University, Japan, and Mount Kenya University, Kenya.

#### Plans for communicating important protocol amendments to relevant parties (e.g., trial participants, ethical committees) {25}

Decisions on important trial amendments must be made through a formal procedure and will be approved by institutional review boards (IRB) at Mount Kenya University and Osaka Metropolitan University. The protocol in the clinical trials registry will also be updated accordingly.

#### Dissemination plans {31a}

The results will be shared with the Homa Bay County government and Kenya National Malaria Control Program and discussed for the possibility of expanding the program. Also, the results will be disseminated through publications and conferences to help the development of novel malaria control strategies in other malaria-endemic countries. The feedback from the research participants will also help shape the future improvement of the intervention and acceptance by the communities.

## Discussion

Widespread adoption of LLIN has been cited as the most significant contributor to the decrease of malaria in sub-Saharan Africa between 2000 and 2015 [31]. However, insecticide resistance in *Anopheles* vectors, inadequate LLIN coverage, and non-compliance to LLIN hinder the effectiveness of LLIN. Olyset®Plus LLIN incorporates the synergist PBO to restore the insecticidal effect of permethrin against mosquitoes with metabolic resistance to the pyrethroid. By retrofitting Olyset®Plus LLIN into a ceiling net to protect those who are not covered by conventional LLIN, Olyset®Plus ceiling nets may represent an additional tool that can complement existing interventions to further reduce malaria transmission.

Ceiling nets have the potential to be more durable and sustainable than conventional LLIN. In our study area, many schoolchildren sleep on the floor [7], which makes the permanent installation of conventional LLIN difficult since it likely impedes movement within the house. Daily or frequent handling of LLIN may increase the risk of damage to it. Long-term observations from the previous ceiling net study [14] suggest that the overall physical integrity of the ceiling net is quite high even after 5 years, and even though the effect of the insecticide in the ceiling net is limited to 3 to 5 years [32], the physical protection provided by the ceiling net may still provide additional advantages over the use of conventional LLIN alone. Additional cost-effectiveness analyses and long-term observational studies on ceiling net durability will be useful to guide the adoption of this novel tool in the future.

As is typical of the wider Lake Victoria region of western Kenya, iron sheets are the most popular roofing material in our study area on Mfangano Island [23]. However, a variety of roof and house designs of various sizes makes the installation of ceiling nets a labor-intensive process. Using Olyset®Plus sheets 6 × 8 m or 4 × 6 m in size, it takes a team of three to four experienced installers approximately an hour to install the ceiling net in a typical house with a hip or tented roof. In this study, we provide training to CHVs and other village volunteers on ceiling net installations. If ceiling nets become more widely adopted in the future, an installation by experienced local volunteers or modification of the design should reduce the cost of implementation.

Communication with the community members is another key aspect of this trial. LLIN has been freely distributed to the communities every 3 years for more than a decade. Therefore, many residents may expect the same for the ceiling nets if the latter proves to be effective. Since ceiling nets are visible to all study participants, achieving adherence for 1 year, especially among participants in the control group, will be challenging. To encourage participant retention, a stepped wedge design that enables all households in the control arm to receive ceiling nets at the end of the 1-year follow-up period is planned after this trial. Since 2012, members of the research team have conducted collaborative community-based research projects with the local government and health authorities, stakeholders, and community gatekeepers in the study area [26, 33–35]. Good rapport with local community members is crucial to secure their participation in this study.

This study has several limitations. First, the visible nature of the ceiling net makes it impossible to blind study participants and field research staff. However, microscopists and laboratory technicians who process and analyze samples are blinded to the study arm assignment of participants. Indoor resting mosquitoes will be collected by pyrethrum spray catches and CDC light traps to determine vector density, which should be free of assessor bias. Second, since we hypothesize that schoolchildren will benefit the most from the additional protection of the ceiling net, our primary outcome is the prevalence of *Plasmodium* infections in children aged 3 to 15 years old. This will be assessed by school-based cross-sectional surveys. However, the benefit of the ceiling net will likely be extended to other age groups who share the same dwelling units. While we plan to examine the impact in a longitudinal cohort, the present cohort is small relative to the scale of the intervention. As such, findings in this cohort may not be generalizable to the trial population. Third, given that the ceiling nets are visible and thought to function in ways similar to conventional LLIN, it is conceivable that participants in the intervention arm may lower their usage of conventional LLIN, effectively relying on the ceiling net as a replacement rather than an addition to conventional LLIN for malaria protection. Continuous community engagement throughout the trial period will help to reinforce the importance of consistent LLIN use. Bi-weekly interviews with cohort participants will provide data on the pattern of LLIN use after ceiling net installation. We will conduct surveys and in-depth interviews to elicit participants’ perceptions of the ceiling net, which can guide future messaging and implementation.

Improving housing and the built environment, including screened windows, doors, or eaves to reduce malaria transmission, has long been proposed [15, 36]. However, there has been only a handful of trials on house modifications for preventing malaria [17], and only two have focused on the impact of screening of the ceiling on malaria prevalence [13, 14]. This study will be the first trial to evaluate the impact of ceiling nets on the infection incidence by active case detection, as submicroscopic or/and asymptomatic infections represent a known but not well-understood source of residual transmission. The results from this study will inform decision-makers about the wider adoption of ceiling nets as another tool in the next generation of vector control.

## Trial status

Recruitment started on September 1, 2021, and the final subject enrollment was completed on October 10, 2021. The follow-up of the cohort has been completed on December 16, 2022. The focus group discussion and questionnaire survey for the perception, as a final data collection, is planned for April 2023 (Table 3). The current protocol is version 2.1 as of June 22, 2021. The study was initially intended to be a stepped wedge trial; however, the authors agreed that the study should be published as a stand-alone cluster randomized controlled trial; thus, submission of this protocol was delayed.

**Table 3 Tab3:** Trial status and plan

Action	Date
Anticipated date of first enrollment	September 1, 2021
The actual date of the first enrollment	September 23, 2021
Finalize the enrollment	October 10, 2021
Start the implementation of the intervention	November 22, 2021
Finalize all the implementation	January 21, 2022
Start the first sampling in the cohort	December 9, 2021
Complete all follow-ups in the cohort	December 16, 2022
Complete cross-sectional malaria survey	February 24, 2023
Qualitative data collection (completion of the data collection) (expected)	April 2023

## Data Availability

The study regimes, consent forms, assent forms, and study-related materials are accessible from the corresponding author. The final trial dataset will be available to all investigators. The corresponding author will make the de-identified datasets available upon reasonable request.

